## Population for Analysis

The following populations will be considered for the analyses:

- Intention to treat (ITT) population: Includes all randomized participants, regardless of protocol adherence.
- Per-protocol population (PP): Includes all randomized participants showing full protocol adherence.
- Safety population: Includes all subjects who have received at least one dose of study medication. Subjects who withdraw from the study will be included in the safety analysis. A list of withdrawn subjects, preferably with the reasons for withdrawal, will be made.

## Statistical Analysis

Statistical analysis will be performed by Unit for Applied Research, NTNU.

Descriptive data will be presented as mean ± SD. Dichotomuos outcome variables will be compared using non-parametric test (paired Wilcoxon signed rank test, and McNemar´s test). P-values <0.05 will be considered significant.

0-hypothesis: Oxytocin nasal spray does not differ from placebo in reducing alcohol withdrawal symptoms or decrease craving after detoxification

Primary hypothesis 1: Oxytocin nasal spray can reduce the amount of oxazepam needed to complete 3 days of alcohol detoxification.

Primary hypothesis 2: Oxytocin nasal spray can decrease craving the subsequent 4 weeks after detoxification.

Group comparisons of oxazepam use (measures in mg) at 3 days will be done with student t-test. We will use mixed‐effects regression analyses to examine the change in sleep and actigraph scores from D1 to D3, and changes in anxiety, depression and alcohol use from discharge (D3) to follow-up (D30). Statistics will be performed with per-protocol and intention-to-treat data.Mixed methods take the correlation among repeated measures into account, and they use all available data, thereby lessening concerns about missing data. The basic model will include group (oxytocin, placebo) as the between‐subjects factor and time as the repeated measure. The treatment effect will be evaluated as the group by time interaction, according to the planned comparisons. Both group and time will be fixed‐effects. Covariates can also be added to the models, in order to partial out their effects before evaluating the treatment effects. Follow‐up t‐tests and other post hoc methods will be used to test more time‐ and group‐specific hypotheses. We will test primary hypotheses at the .05 level of significance, but follow‐up and exploratory analyses will be tested at the .01 level of significance.

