
## Rationale for the Study and Purpose

The study will be conducted at Lade Addiction Treatment Center, Norway. 40 consecutively admitted in-patients undergoing medical detoxification from alcohol at Lade Addiction Treatment Center will be included in the study. In 2014, 150 patients with alcohol dependency as their primary diagnosis were admitted electively to the detoxification unit. If the enrollment of the target number of inclusions exceeds 12 months, the study will seek to include patients from the Clinic of Substance Use and Addiction Medicine at St. Olav’s Hospital.

Oxytocin is neuropeptide hormone which, to our knowledge, is not associated with severe adverse effects. It is a world-wide used, approved, licensed and recommended medicine indicated for the initiation or improvement of uterine contractions in order to achieve vaginal delivery for fetal or maternal reasons. Oxytocin nasal spray is also commonly used by mothers when breastfeeding in the therapy and prophylaxis of mastitis. The potential benefits of the drug as an alternative to benzodiazepine against alcohol withdrawal symptoms, and the benefits of the study are considered greater than the health risks.

In a double blind, prospective randomized parallel group placebo-controlled trial patients will be assigned to receive either oxytocin or placebo which will be administered as a nasal spray twice daily during 3 days of inpatient detoxification, and as a self-administrated spray during a 4-week follow-up period. One arm will receive oxytocin nasal spray, the other arm placebo spray. Patients are randomized in a 1:1 ratio to oxytocin or placebo. The oxytocin will be administered as Syntocinon nasal spray. Syntocinon contains synthetic oxytocin for intranasal use containing 6.7 μg per dose. 1 IU varies between 1.7 μg and 2.2 μg. With 1 IU = 1.7 μg, 1 μg = 0,588 IU, which makes 6.7 μg = 4.34 IU, for practical use 4 IU per dose. We are planning to use 6 insufflations and in total 24 IU given twice daily. This is the same dose of oxytocin as given in a pilot study on human subjects, in which no adverse side effects were reported. The oxytocin dose used by breast-feeding mothers is 6.7 μg.

The placebo spray contains the same ingredients as Syntocinon, except oxytocin.

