# Overall STUDY Design

The study is a phase III.

Double blind, prospective randomized parallel group placebo-controlled trial.

4 weeks outpatient treatment

Day 1-3: In-patient

treatment

On admission

____________________________________________________________________________________________
Main assessments Study entry Discharge Follow-up
 D0 D2 D3 D30 + D60

Arm 2:Placebo

Arm 1: Oxytocin

| Study Period | Estimated date of first patient enrolled: 01.10.2016  Anticipated recruitment period: 12 months  Estimated date of last patient completed: 01.10.2017 |
| --- | --- |
| Treatment Duration: | 3 days in-patient treatment, followed by 4 weeks outpatient treatment and a phone interview at 8 weeks. |
| Follow-up: | Check-point at 4 weeks during 4-week outpatient treatment, phone interview at 8 weeks |

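### Section 10.4 names only paired tests for dichotomous outcomes, but the two arms are unmatched patients, so a between-arm binary comparison has no defined pairs

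*Protocol*

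**What the plan says.** Section 10.4 (Statistical Analysis) gives one sentence on binary outcomes: "Dichotomuos outcome variables will be compared using non-parametric test (paired Wilcoxon signed rank test", to which it adds McNemar's test. It names no other test for them.

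The design is stated in section 3 as "Double blind, prospective randomized parallel group placebo-controlled trial". Section 1.4 adds "One arm will receive oxytocin nasal spray, the other arm placebo spray" and "Patients are randomized in a 1:1 ratio to oxytocin or placebo". The protocol describes no crossover, matching or other pairing of patients.

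The null hypothesis in section 10.4 is a contrast between arms: "Oxytocin nasal spray does not differ from placebo in reducing alcohol withdrawal symptoms".

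Elsewhere the same section treats the arms as independent. For the oxazepam endpoint it says "Group comparisons of oxazepam use (measures in mg) at 3 days will be done with student t-test". For repeated measures, "The basic model will include group (oxytocin, placebo) as the" between-subjects factor.

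**The concern.** McNemar's test and the signed-rank test work on differences within a pair, meaning the same patient measured twice or two deliberately matched patients. Between the oxytocin and placebo arms there are no such pairs. An analyst following the sentence literally would have to invent them, for example by row order or enrolment order, and the p-value would then reflect that choice as well as the data. If the arms end with different numbers, the unpaired remainder must be left out. That conflicts with the intention-to-treat population in section 10.3, which takes in everyone randomized.

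The signed-rank test adds nothing here. For a two-valued variable every non-zero paired difference has the same absolute size, so the test reduces to the sign test, which is in substance McNemar's test. The sentence thus names one paired method twice and no unpaired method.

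At stake are binary between-arm comparisons such as relapse to drinking by day 30, an item recorded in the flow chart (section 6.1, Table 1).

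**Working it through.** **1. The plan's own figure.** The protocol gives no figure for a binary outcome. Its one sample-size figure (section 10.1) is 16 per group for a 10 mg difference, SD 10 mg, alpha 0.05 and power 80%. The formula for two independent means, two-sided, gives

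n per arm = 2 × (1.960 + 0.842)² × SD² / difference² = 2 × 7.85 × 100 / 100 = 15.7, rounded up to 16.

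This matches, so the sample size treats the arms as independent groups.

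**2. One data set, many McNemar results.** The counts are assumed, because the protocol gives none: 8/20 events in one arm and 14/20 in the other (40 patients at 1:1 gives 20 per arm). Tests for independent groups give one answer each:

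- Pearson: pooled proportion 22/40 = 0.55; SE = √(0.55 × 0.45 × 2/20) = 0.157; z = 0.30/0.157 = 1.91; p = 0.057.
- Fisher's exact test: p = 0.111.

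For McNemar, let k be the number of pairs in which both patients have the event. The margins allow k from 2 to 8. The discordant pairs are 8 − k and 14 − k, and the exact p-value is 2 × P(X ≤ 8 − k) with X binomial(22 − 2k, ½). If pairs are formed at random, k is hypergeometric: P(k) = C(14,k) × C(6,8−k) / C(20,8), with C(20,8) = 125,970.

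| k | Discordant pairs | Exact McNemar p | Share of random pairings |
|---|---|---|---|
| 2 | 6, 12 | 0.238 | 91/125,970 = 0.07% |
| 3 | 5, 11 | 0.210 | 2,184/125,970 = 1.7% |
| 4 | 4, 10 | 0.180 | 15,015/125,970 = 11.9% |
| 5 | 3, 9 | 0.146 | 40,040/125,970 = 31.8% |
| 6 | 2, 8 | 0.109 | 45,045/125,970 = 35.8% |
| 7 | 1, 7 | 0.070 | 20,592/125,970 = 16.3% |
| 8 | 0, 6 | 0.031 | 3,003/125,970 = 2.4% |

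The same 40 outcomes can fall on either side of 0.05, but only 2.4% of random pairings fall below it. About 68% (k = 5 or 6) give 0.109 or 0.146, near Fisher's value.

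**3. Error rate and power under random pairing.** Simulation of 20 v 20 independent binary outcomes, 40,000 runs per setting, with assumed event rates:

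| Setting | Exact McNemar | Fisher | Chi-square McNemar | Pearson |
|---|---|---|---|---|
| Type I error (equal rates 0.3, 0.5, 0.7) | 0.020–0.023 | 0.020–0.024 | 0.041–0.044 | 0.042–0.053 |
| Power, 0.5 v 0.2 | 0.365 | 0.408 | 0.469 | 0.529 |
| Power, 0.7 v 0.3 | 0.592 | 0.598 | 0.688 | 0.715 |

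Type I error is not inflated. In these two settings the power loss is about 1 to 4 points for the exact tests and 3 to 6 for the chi-square versions.

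**4. Unequal arms.** With 21 v 19, for example, at most 19 pairs can be formed and 21 − 19 = 2 randomized patients drop out of the test.

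**5. Within-arm use.** Suppose the tests were applied in each arm over time, with the same true change in both arms (assumed event rate 0.9 falling to 0.6, visits simulated as independent, 20 per arm). Each arm is significant with probability 0.433, so exactly one arm is significant in about 2 × 0.433 × 0.567 = 49% of trials (simulated: 49%). That pattern says nothing about a difference between oxytocin and placebo.

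**The case against.** The strongest defence is that the sentence does not say the comparison is between arms. Section 10.4 speaks of group comparisons when it turns to oxazepam, and several measures are repeated within patients on days 2, 3 and 30, where McNemar's test can be legitimate. On that reading the protocol merely leaves the between-arm binary test to the SAP. This stands in part: a within-patient use would not be wrong in itself. It does not rescue the sentence, because the stated hypotheses set oxytocin against placebo, a within-arm test cannot address that, and the text never limits itself to change over time.

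Three stronger readings are tempting, and the document does not support them.

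- A reader might infer that the main results are compromised. They are not. Oxazepam has a t-test between groups, the repeated measures have mixed models with treatment group as a factor, and relapse and drinking appear among the endpoints (section 2.1) as a time and an amount. The flow chart counts binge episodes, section 8.5.4 only has adverse events discussed in the study report, and need for any oxazepam is not defined as an outcome.
- A reader might infer a raised false-positive rate. Under random pairing there is none.
- A reader might take 0.031 to 0.238 as the typical spread. Those are the extremes, with probabilities of 2.4% and 0.07%.

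**Conclusion.** The sentence is wrong as written. This is a method the protocol fixes, so it is more than detail left for the SAP. Read as a between-arm comparison, it has no defined pairs, an arbitrary p-value and no way to keep all patients when arms are unequal. Read as within-arm, it does not test the treatment. On neither reading does section 10.4 supply a valid between-arm test for a binary outcome.

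The size is modest. In the illustration the p-value can run from 0.031 to 0.238 against Fisher's 0.111, mostly lying between 0.11 and 0.15, with some loss of power and no excess of false positives. These figures rest on assumed counts and event rates with 20 patients per arm. Because no listed primary or secondary endpoint is explicitly binary, this is something that should be fixed; it does not threaten the trial's main analyses.

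**What to change.** Delete both paired tests from section 10.4 and replace the sentence with:

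*Dichotomous outcomes will be compared between arms with a test for independent groups (e.g. Fisher's exact or an unconditional exact test), reported with the risk difference and 95% CI.*

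Leave the oxazepam t-test and the mixed models as stated. In particular, do not add a general rank-test rule for ordinal or skewed outcomes in the same edit, since it could conflict with those analyses.

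The cost is one sentence in a protocol amendment. Sample size, visits and data collection do not change. Making the change before unblinding removes any later choice of pairing or of substitute test.

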## Dosage and Drug Administration

Information on spray pattern and distribution provided by the trade agency company is attached in appendix A.

Phase 1: 3-day detoxification with 1 dose x 2 daily. Each test dose consists of 6 insufflations of Syntocinon Spray or placebo, with each insufflation given 15 sec apart and alternating between nostrils. Each insufflation consists of 6.7 μg oxytocin.The first intranasal dose of the test substances will be administrated immediately after group allocation. Patients are given instruction in proper intranasal self-administration techniques during their first dose. Instructions of priming and use is also noted in the notebook the participants are given. The second dose is taken at 1800h on admission day. The following two days (day 2-3) the patients will take their intranasal doses at 0900h and at 1800h under supervision. Patients will also be wearing an actigraph during detoxification which will register akathisia and sleep in an inpatient setting.

Phase 2: Patients completing the 3 day oxytocin or placebo detoxification trial, are discharged to a 4 week trial of self-administrated intranasal spray (as needed), with maximum use 2 insufflations x 3 daily in order to reduce alcohol cravings or consumption. Staff and patients will be instructed in priming the nasal spray by completing 5 test sprays before first use as well as 1-3 sprays later on, before administering the spray.

The following specific instructions will be given to the staff and the patients^21^:

1. Use the head upright position in standard practice but allow patients to choose the most comfortable position for themselves.

2. Do not administer if the nose is heavily congested and clear the nose from obvious obstruction before administering.

3. Ensure the bottle is primed. To do so, complete 1-3 test sprays as needed before each dose, until a fine mist can be seen and the spray is ready for use.

4. Close one nostril with one finger while administering the spray to the other nostril. Upon delivery of the medication, inhale and breathe in lightly.

5. Insert bottle 1 cm into the nostril and encourage an administration vertically into the nostril.

6. Alternate administrations between nostrils, 15 seconds between each spray.

7. Keep dust cap on whenever nasal spray is not in use.

Both the staff and the patients will be given hands-on training related to this procedure before administration of the product.

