### Treatment Start, D1

Since patients are likely to experience alcohol abstinence, they will undergo CIWA-Ar registrations as described in section 7.2. Medication for abstinence (benzodiazepines in the form of oxazepam) is given based on CIWA-Ar-scores. Study subjects will receive the first dose of nasal spray shortly thereafter, while following the standard procedures for abstinence treatment. Study subjects receive the Actigraph to be carried throughout the stay.

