# assessments

## Assessment of Efficacy Response

Efficacy response is measured as the total number of mg of oxazepam used by study subjects undergoing detoxification based on a symptom-driven protocol using CIWA-Ar scores (see Section 7.2). The dosages of oxazepam and the CIWA-Ar-scores are registered in the CRF.

Actigraph-assessed akathisia and self-reported sleep will also be compared with CIWA-Ar scores and oxazepam dosages retrospectively.

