**CIWA-Ar**

CIWA-Ar has 10-items assessing headache, visual and tactile and auditory disturbances, paroxysmal sweats, orientation and clouding, agitation and anxiety (all assessed on a 0-7 severity scale). It also includes blood pressure, pulse, respiration rate, temperature. A symptom-driven protocol of PRN administrations of oxazepam will be followed to all included patients while undergoing detoxification. Symptom-triggered benzodiazepine treatment has been shown to require less total medication compared to fixed regimen benzodiazepine tapers ^22^. A ‘‘standing order set’’ to administer oxazepam based on a patient’s CIWA-Ar score will as such be followed. Mild CIWA-Ar scores (0 to 9)^3^ indicate mild withdrawal symptoms and indicate no benzodiazepine treatment (reassessed in 4 hours). A CIWA-Ar score of 10 to 14 represents moderate withdrawal and 10 mg oxazepam will be given orally as needed, scores reassessed after 1 hour. Severe withdrawal is represented by a score 15 and above and indicate oxazepam 15 mg given orally as needed, scores reassessed after 1 hour. All benzodiazepines (dosage and amount) will be documented along with CIWA-scores.

Laboratory evaluation:

St. Olav’s University Hospital, department of medical biochemistry will be used for the analysis of hematology and biochemistry specimens collected, except plasma-oxytocin which is sent to the Hormonlaboratoriet at Oslo Universitetssykehus.

Hematology assessments will include the following parameters: hemoglobin, platelets, CRP, HCT, WBC (incl.differential counting,

Blood chemistry assessments will include the following: albumin, creatinine, Na, K, Ca, glucose, ALAT, LD, ALP, γGT, INR, bilirubin, p-oxytocin, CDT, PEth, HCG (in fertile women).

Urine analysis will include a toxicological screening including ethanol metabolites - EtG and EtS.

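### The primary oxazepam comparison is an unadjusted t-test that leaves out the arrival CIWA-Ar score, giving up precision the trial could have from data it already collects

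*Protocol*

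**What the plan says.** Section 10.4 names the test for the oxazepam endpoint: "Group comparisons of oxazepam use (measures in mg) at 3 days will be done with student t-test". The same section then describes mixed-effects models for sleep, actigraph scores, anxiety, depression and alcohol use, and adds: "Covariates can also be added to the models, in order to partial out their effects". That sentence belongs to the mixed models, is optional and names no covariate.

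Section 7.1 defines the endpoint: "Efficacy response is measured as the total number of mg of oxazepam used by study subjects undergoing detoxification". It also says that oxazepam doses and CIWA-Ar scores are both entered in the CRF.

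Section 7.2 ties dose to score. Scores of 0 to 9 lead to no benzodiazepine. For the next band, "A CIWA-Ar score of 10 to 14 represents moderate withdrawal and 10 mg oxazepam will be given orally as needed". Scores of 15 and above lead to 15 mg.

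The flow chart in Section 6.1 lists CIWA-Ar on arrival (D1). Section 6.2.1 gives the order on that day: CIWA-Ar is scored, then "Medication for abstinence (benzodiazepines in the form of oxazepam) is given based on CIWA-Ar-scores", then "Study subjects will receive the first dose of nasal spray shortly thereafter, while following the standard procedures for abstinence treatment". Section 5.2 adds: "The first intranasal dose of the test substances will be administrated immediately after group allocation".

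**The concern.** The outcome is a sum of doses, each triggered by a CIWA-Ar score. The first score in that series is available before any study drug and is a natural baseline covariate. Section 4.4 sets no minimum score, so severity on arrival can vary, and Sections 10.2 and 10.2.1 describe no stratification by it.

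With 20 per arm, the difference between arms in mean arrival score has a standard error of sqrt(2/20) = 0.32 SD. At an assumed correlation of 0.5, an imbalance of that size moves the oxazepam estimate by 0.32 × 0.5 × 10 mg = 1.6 mg, against a target of 10 mg. The t-test treats this movement as noise; an adjusted analysis removes much of it.

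A smaller question concerns the endpoint window. Section 6.2.1 read with Section 7.1 suggests that oxazepam given before the first spray may enter the total. The study drug could not have influenced such doses.

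**Working it through.** **Inputs from the protocol.** Difference 10 mg, SD about 10 mg, alpha 0.05, power 80%, 16 per group, 40 in total (Section 10.1); 1:1 allocation (Section 1.4), hence 20 per arm. Two-sided testing is assumed because Section 10.1 does not state sidedness.

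**Inputs not in the protocol.** The correlation r between arrival CIWA-Ar and the 3-day total, and the distribution of any pre-spray dose. Both are assumed and varied.

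**Step 1: the plan's own figure.** n per arm = 2 × (1.96 + 0.84)² × (10/10)² = 15.7, rounded up to 16. This matches Section 10.1.

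**Step 2: power of the planned test.** Noncentrality = 10 / (10 × sqrt(2/20)) = 3.16 on 38 degrees of freedom. Power is 86.9%.

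**Step 3: power with arrival CIWA-Ar as covariate.** Residual SD = 10 × sqrt(1 − r²); noncentrality = 10 / (residual SD × sqrt(2/20)); 37 degrees of freedom. The equivalent unadjusted total is 40 / (1 − r²). The last column allows for the average cost of chance imbalance in the covariate by multiplying the variance by 1 + 1/36.

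| Assumed r | Residual SD (mg) | Noncentrality | Power | Equivalent total N | Power with imbalance cost |
|---|---|---|---|---|---|
| 0 | 10.00 | 3.16 | 86.85% | 40 | 85.9% |
| 0.2 | 9.80 | 3.23 | 88.2% | 42 | 87.3% |
| 0.3 | 9.54 | 3.31 | 89.8% | 44 | 89.0% |
| 0.5 | 8.66 | 3.65 | 94.5% | 53 | 93.9% |

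The difference detectable with 80% power falls from 9.1 mg unadjusted to 8.9, 8.7 and 7.9 mg at r = 0.2, 0.3 and 0.5 (without the imbalance cost).

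**Step 4: would dropping pre-spray doses help?** Let pre-spray mg have SD s and correlation c with later mg, and let the total have variance 100. The later SD x solves x² + 2csx + s² = 100. Take s = 5 mg, which is what results if half the patients receive one 10 mg dose.

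- c = 0: x² = 75, x = 8.66 mg, power 94.5%.
- c = −0.3: x = 10.29 mg, power 85.0%.
- c = −0.5: x² − 5x − 75 = 0, x = (5 + sqrt(325))/2 = 11.5 mg, power 76%.

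Exclusion alone can therefore help or harm. With pre-spray mg as a linear covariate, the estimated treatment effect is the same whether the outcome is total or post-spray mg, so the result does not depend on c in this way.

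**The case against.** The strongest reply is that nothing here is an error. Randomization makes the unadjusted t-test valid, its standard error already reflects chance imbalance, and on the protocol's own inputs it has about 87% power against a stated 80%. All of that stands. A reader might infer that the primary result would be biased or the trial underpowered; the protocol supports neither. Covariates are often left to a statistical analysis plan, but here the protocol itself names the primary test without one.

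Second, the correlation is unknown and may be modest. Section 4.4 excludes only patients who have no alcohol in the blood and last drank more than 15 h ago, so enrolled patients arrive with alcohol in the blood or within 15 h of drinking. Section 1.1 says symptoms can appear up to 72 hours after the last intake. The arrival score may therefore precede peak withdrawal. This stands too: the score cannot be called a strong predictor on the evidence here, and at r = 0.2 the gain is slight.

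Third, a reader might infer from Section 6.2.1 that pre-spray oxazepam is certainly counted, and that removing it would strip out a large share of the variance. No sentence says it is counted. Section 6.2.1 can also be read as the spray starting alongside symptom-triggered care, and Section 5.2 ties the first spray only to allocation. A large variance saving needs both frequent pre-spray dosing and no negative correlation with later doses; the protocol gives neither. What remains is that the start of counting is not stated.

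**Conclusion.** The point holds as an avoidable loss of precision in the primary comparison. The sample size calculation is sound and the planned test is valid. Adjusting for the arrival score would raise power from 86.9% to 88.2%, 89.8% or 94.5% at correlations of 0.2, 0.3 or 0.5, or to 87.3%, 89.0% or 93.9% once chance imbalance in the covariate is costed. If the score is uninformative, power is 86.85% on the simple calculation and about 85.9% on the stricter one. The exchange is favourable unless the correlation is near zero. That is unlikely where score-triggered dosing generates the outcome, but it cannot be established from the protocol.

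These figures rest on an SD of 10 mg, a true difference of 10 mg, 20 analysed patients per arm and a linear relation with the score. The pre-spray question is secondary: it calls for a definition of the counting window, and no size can be put on it from the protocol.

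**What to change.** In Section 10.4, make the primary analysis an ANCOVA of the 3-day oxazepam total with arm as factor and the first CIWA-Ar score on arrival as a pre-specified covariate. Define that score as the one taken before any oxazepam or spray, since a reassessment after oxazepam would no longer be the arrival score. Keep the Student t-test as a sensitivity analysis. For this comparison, the named covariate should take the place of any open-ended option to add others.

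In Section 7.1, state the time from which oxazepam is counted. If doses before the first spray are included, enter pre-spray mg as a further pre-specified covariate; do not simply subtract them. Because that dose follows the CIWA-Ar bands, it will overlap with the arrival score and may add little.

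The cost is wording plus one degree of freedom for the CIWA-Ar score, and one more if pre-spray mg is added. Dose times relative to the first spray would be needed for the second covariate. No extra patients or assessments are required, and no treatment rule changes.

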# STUDY OBJECTIVES and related endpoints

## Primary Endpoint

| Phase 1: Milligrams of benzodiazepines (oxazepam) used to complete 3 days of detoxification and Actigraph-assessed akathisia and sleep.  Phase 2: Time to ‘relapse’ and amount of alcohol intake during 4 weeks of subsequent outpatient treatment. |
| --- |

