# STUDY procedures

## Flow Chart

Table 1. Trial flow chart

|  | **In-patient period (day)** | | | **Outpatient Period (day)** | |
| --- | --- | --- | --- | --- | --- |
| **Time** | **On arrival**  **D 1** | **D 2** | **Discharge**  **D 3** | **D 30** | **D 60** |
| Informed consent | X |  |  |  |  |
| Inclusion/exclusion  Evaluation | X |  |  |  |  |
| Medical History, record of concomitant medication | X |  |  | X |  |
| Prior treatment | X |  |  |  |  |
| Physical Examination^1)^ | X |  |  |  |  |
| Vital signs, CIWA-Ar ^2)^ | X | X | X | X |  |
| Blood samples^3)^ | X |  | X | X |  |
| Urine samples^4)^ | X |  | X | X |  |
| Actigraph | X | X | X |  |  |
| Staff administered nasal spray | X | X | X |  |  |
| Self-reported sleep | X | X | X | X |  |
| Alcohol Craving Experience Questionnaire(ACE), SCL-10, PAM-13^5)^ |  |  | X | X |  |
| RMET^6)^, dot-probe-task^7)^ |  | X | X | X |  |
| Self-administered and reported use of nasal spray, relapse to drinking and weighing of spray bottles |  |  |  | X |  |
| Alcohol consumption (Time-Line Follow-back^8)^, Days until relapse, Daily quantity of standard alcohol units, Number of binge drinking episodes, self-reported intake of benzodiazepines |  |  |  | X |  |
| Phone interview with AUDIT^9)^ |  |  |  |  | X |

1. Cor/pulm/abdomen and peripheral lymph node status and neurology with emphasis on alcoholic damage to the cerebellum and signs of Wernicke/Korsakoffs syndrome.
2. Blood pressure, pulse, temperature, weight, alcohol expiration test until 0‰ x 2. CIWA-Ar after symptom driven protocol
3. Once daily: CRP, Hb, HCT, WBC (incl.differential counting, Na, K, Ca, glucose, creatinine, ALAT, LD, ALP, γGT, INR, albumin, bilirubin, p-oxytocin, CDT, PEth.
4. Once daily: Toxicology screening: urine dipstick and laboratory tests (incl. the ethanol metabolites EtG and EtS. (Pregnancy test (HCG) at admittance in fertile women).
5. See chapter 7.3 Other assessments
6. See chapter 7.3 Other assessments
7. See chapter 7.3 Other assessments
8. See chapter 7.3 Other assessments
9. See chapter 7.3 Other assessments

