### During Treatment, D1-D3

CIWA-Ar registrations are performed to monitor abstinence severity; these measturements include blood pressure and heart rate. Since CIWA-Ar is symptom driven, there are no exact times for these measurements. Nasal spray is given twice daily, at 0900h and at 1800h. The nasal spray container is weighed at the end of the inpatient period.

Day 3; at discharge: Actigraphs are handed in. Blood and urine samples are obtained. Patients are asked to fill out questionnaires at day 3, see table in section 7.3. Patients are instructed in the use of nasal spray as needed for the next 4 weeks. They will receive a notebook in which they will keep a log of use of the study drug, any intake of concomitant medication etc., and possible adverse events.

### End of Treatment and End of Study Visit, D 30

Clinical status with vital signs and laboratory tests is repeated. Patients fill out questionnaires (see table in section 7.3), and hand in nasal sprays and their notebooks. Nasal spray containers are weighed. A phone interview will be done at day 60.

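### The actigraph records only two nights, both on treatment, so the planned D1-to-D3 group-by-time test for actigraphic sleep reduces to night 2 versus night 1 and cancels any effect equal on both

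*Protocol*

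**What the plan says.** Section 2.1 lists "Actigraph-assessed akathisia and sleep" beside oxazepam use as the phase 1 primary endpoint.

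Section 10.4 plans mixed-effects regression to "examine the change in sleep and actigraph scores from D1 to D3", with group and time as fixed effects. It adds: "The treatment effect will be evaluated as the group by time interaction".

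On collection:
- Section 6.2.1: "Study subjects receive the Actigraph to be carried throughout the stay".
- Section 6.2.2: "Day 3; at discharge: Actigraphs are handed in".
- Table 1 marks the device on the three inpatient days only ("Actigraph | X | X | X"). Self-reported sleep is a separate row with a further entry at D30 ("Self-reported sleep | X | X | X | X").

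Section 5.2 gives the first spray dose directly after allocation on the admission day, and then: "The second dose is taken at 1800h on admission day".

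**The concern.** A change from D1 to D3 tested as group by time suits a measure with a value before treatment and later values on treatment. The actigraph schedule does not supply that for sleep. The device goes on when treatment starts, so no night is recorded before the first dose, and it comes off before a third night. What remains is a comparison of two treated nights.

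At stake is the reading of an endpoint listed as primary. If oxytocin improved sleep from the first night and kept doing so, the planned test would be expected to show nothing, and that result could be reported as no effect on sleep. Activity has a lesser difficulty: D1 and D3 are part-days of wear, so daily totals are not on the same footing as D2.

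**Working it through.** **Nights recorded.** Wear runs from treatment start on D1 (section 6.2.1) to discharge on D3 (section 6.2.2). Whatever the clock times of arrival and discharge, that span holds two nights, D1/D2 and D2/D3. Labelled by bedtime, D3 has no night. Labelled by day of waking, D1 has none. No labelling gives three whole nights.

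**Treatment status of those nights.** The first dose follows allocation on D1, and another is due at 18:00 that day (section 5.2). Both nights therefore come after dosing has begun.

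**What the interaction estimates.** Let τ1 and τ2 be the oxytocin-minus-placebo effects on nights 1 and 2.
- Group by time: (night 2 − night 1, oxytocin) − (night 2 − night 1, placebo) = τ2 − τ1.
- Arm difference over both nights: (τ1 + τ2)/2.

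If τ1 = τ2 = τ, the first quantity is 0 and the second is τ.

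**Size.** The protocol gives no SD for actigraphic sleep, so these inputs are assumptions: between-patient SD 0.7, within-patient SD 0.7, and 20 patients per arm (the 40 planned, 1:1).
- SD of one night = √(0.49 + 0.49) = 0.99, so an effect of 1.0 is about 1 SD.
- SD of the two-night mean = √(0.49 + 0.49/2) = 0.857.
- SD of the night 2 − night 1 change = √(2 × 0.49) = 0.99.

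Power of a two-sided t-test at 0.05:

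| Effect on night 1, night 2 | Interaction: standardised effect, power | Two-night mean: standardised effect, power |
| --- | --- | --- |
| 1.0, 1.0 | 0/0.99 = 0, 5% | 1.0/0.857 = 1.17, 95% |
| 0.5, 1.0 | 0.5/0.99 = 0.51, 34% | 0.75/0.857 = 0.87, 77% |

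A simulation of the first row (10,000 runs) rejected the interaction in 4.9% of runs, in agreement with the formula.

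**Wear time.** The protocol gives no arrival or discharge hours. Arrival is assumed between 09:00 and 17:00. Discharge is assumed between 18:00 and 20:00, after the supervised evening dose on D3. Wear is then 7–15 h on D1, 24 h on D2 and 18–20 h on D3. A simulation used unscaled totals, the same wear distribution in both arms and no treatment effect. The average D1-to-D3 change was declared significant in 100% of runs, but the group-by-time test rejected in 4.8%. Unequal wear shifts the time trend and adds noise; it does not by itself produce a false arm difference.

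**Sample size.** Section 10.1 is computed on oxazepam: a difference of 10 mg with SD 10 mg gives 2 × (1.96 + 0.84)² × (10/10)² = 15.7, so 16 per group as stated. Nothing in this point alters it.

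**The case against.** The best defence is that labelling nights and scaling for wear are derivation details that a protocol may leave to an SAP, and the SAP is not shown. Taken alone, that is right. A mixed model can also be fitted to two nights per patient. Neither answer rescues the contrast, because section 10.4 itself names the group-by-time interaction as the treatment effect, and no labelling rule supplies an untreated night.

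Sleep in that sentence also covers self-report, which is marked on D1, D2 and D3. If the D1 entry describes the night before admission, its change to D3 has a pre-treatment reference and is a coherent contrast. The protocol does not give the recall period. The point is therefore limited to actigraphic sleep.

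The endpoint's rank is not settled either. Section 2.1 and the synopsis endpoints list actigraphy as primary, but the synopsis objectives put it among the secondary aims. The sample size and the two primary hypotheses do not rest on it.

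Three stronger readings are tempting, and the documents do not support them:
- A reader might infer that D3 sleep is missing for every patient. That holds only if nights are labelled by bedtime; the D2/D3 night ends on D3.
- A reader might infer that the D1-to-D3 change is an artefact of wear time. That needs sleep split at midnight or unscaled daily activity totals, and the protocol states neither.
- A reader might infer a biased arm comparison. That needs wear time to differ by arm, and nothing in this randomised, blinded design indicates that it would.

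The sketch in section 3 labels study entry D0, which might suggest an additional night. Sections 5.2 and 6.2.1 and Table 1 all start treatment and actigraphy on D1.

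**Conclusion.** The point holds for actigraphic sleep. The collection schedule yields two nights, both on treatment, so the stated interaction tests only whether the effect differs between them. A constant effect is invisible to it (rejection at the nominal 5%), and an effect that doubles from night 1 to night 2 is found with about 34% power, against 77% for the two-night mean. These powers rest on the assumed equal between- and within-patient SDs and 20 evaluable patients per arm. The cancellation of a constant effect does not depend on those assumptions. Unequal wear is a secondary matter of noise. The interaction test keeps its type I error, so the harm is lost sensitivity and a misleading null result. The change is worth making because it is cheap and the endpoint is listed as primary.

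**What to change.** - In section 10.4 and Table 1, define actigraphic sleep as night 1 (D1/D2) and night 2 (D2/D3). Take the treatment effect as the arm difference over those two nights, not as the D1-to-D3 interaction. The interaction can stay as a description of whether the effect changes.
- Adjust for the D1 self-report of sleep if it is confirmed to refer to the night before admission.
- Express actigraph activity per worn hour, because D1 and D3 are part-days.

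The cost is wording in two places and a small derivation rule. Actigraphic sleep then has two time points where the schedule suggests three. No new data are needed, and neither the sample size nor any error rate changes.
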